## Abstract

**Background:** Smoking rates among low-income patients are double those of the general population. Access to health care is an essential social determinant of health. Federally qualified health care centers (FQHC) are government-supported and community-based centers to increase access to health care for non-insured and underinsured patients. However, barriers to implementation impact adherence and sustainability of evidence-based smoking cessation within FQHC settings. To address this implementation barrier, our multi-disciplinary team proposes Mi QUIT CARE (Mile Square QUIT
Community-Access-Referral-Expansion) to establish the acceptability, feasibility, and capacity of an FQHC system to deliver an evidence-based and multi-level intervention to increase patient engagement with a state tobacco quitline.

**Methods:** A mixed-method approach, rooted in an implementation science framework of RE-AIM (Reach, Effectiveness, Adoption, Implementation, and Maintenance), will be used in this hybrid effectiveness-implementation design. We aim to evaluate the efficacy of a novel delivery system (patient portal) for increasing access to smoking cessation treatment. In preparation for a future randomized clinical trial of Mi QUIT CARE, we will conduct the following developmental research: (1) Examine the burden of tobacco among patient populations served by our partner FQHC, (2) Evaluate among FQHC patients and health care providers, knowledge, attitudes, barriers, and facilitators related to smoking cessation and our intervention components, (3) Evaluate the use of tailored communication strategies and patient navigation to increase patient portal uptake among patients, and (4) To test the acceptability, feasibility, and capacity of the partner FQHC to deliver Mi QUIT CARE.

**Discussion:** This study provides a model for developing and implementing smoking and other health promotion interventions for low-income patients delivered via patient health portals. If successful, the intervention has important implications for addressing a critical social determinant of cancer and other tobacco-related morbidities.

**Trial Registration:** U.S. National Institutes of Health Clinical Trials, NCT04827420, https://clinicaltrials.gov/ct2/show/NCT04827420.

## Introduction

Smoking rates among adults in the United States are at a 50-year low (14.1%) (1). Despite overall declines in prevalence rates, smoking remains elevated among multiple underserved communities. For example, in Chicago, smoking rates among Blacks are significantly higher compared to whites (25.2 vs. 13.2%, respectively) (2). In urban areas like Chicago, smoking rates are also more pronounced among individuals living at or below the federal poverty level (26.8%) (2). Due to historical and current practices of structural racism, including redlining and community divestment, many Blacks in Chicago reside in neighborhoods characterized by concentrated disadvantage, racial segregation, and poor access to health care (3). Indeed, smoking rates in Chicago community areas with the highest poverty and racial segregation range from 22 to 35% of community residents (2). The negative consequences of smoking are well-established, with smoking contributing to a range of life-limiting conditions, including lung cancer, chronic obstructive pulmonary disease, and emphysema (1). In Cook County, where Chicago is located, lung cancer rates among Blacks are substantially higher than whites (116.9 vs. 81.1 per 100,000 for men and 63.3 vs. 54.7 per 10,000 for women) (2). Further, the all-cause morbidity and mortality due to smoking are higher among low-income and Black smokers due to a high prevalence of illnesses exacerbated by smoking (e.g., diabetes) (4). Combined, these inequalities underscore tobacco use as an urgent public health priority for Chicago and similar urban areas across the United States.

Reduced access to smoking cessation treatments, a key social determinant of health, is a persistent driver of smoking-related health inequalities among lower-income and racial/ethnic minority groups. Federally Qualified Health Care Centers (FQHCs) are safety-net clinics that serve low-income and uninsured patients. A recent study found that the overall proportion of tobacco use in FHQCs across multiple states was 25.8% compared to 20.6% in the general population (5). Mile Square Health Center (MSHC) is a network of FQHCs located in the greater Chicago metropolitan area, including Chicago, Rockford, and Cicero, Illinois. MSHC clinics are located in high-poverty neighborhoods with documented inequalities in lung cancer and other smoking-related health inequalities (i.e., asthma). Given the high levels of tobacco use observed among FQHC patients, health system-wide tobacco cessation interventions can potentially improve health inequalities at the patient's level and the surrounding community areas.

### Tobacco Cessation Treatments

In 2000, the U.S. Public Health Service clinical practice guideline, Treating Tobacco Use and Dependence, recommended that providers consistently identify and document patients' tobacco use status and treat tobacco users via the “5As” framework (Ask-Advise-Assess-Assist-Arrange) (6). Although effective, the 5As model is time-consuming and can be challenging to implement in high-volume clinical settings (7). A simplified version of the framework (Ask-Advise-Refer, [AAR]) was subsequently developed (8). When implemented in clinical settings, AAR has demonstrated effectiveness for increasing patient engagement with recommended treatment approaches such as state tobacco quitlines (9–12). State-run tobacco quitlines offer free telephone counseling and nicotine replacement for low-income smokers. The average quit rates among quitline users are 12.7%, increasing to 28.1% when counseling is combined with nicotine replacement (6). Despite the efficacy of provider interventions such as AAR for linking smokers to treatment, these interventions are underutilized in clinical settings.

FQHCs are required to report annually on their implementation and dissemination of evidence-based tobacco cessation per their Uniform Data Set (UDS) guidelines for FQHCs (5). The Centers for Disease Control and Prevention reports that, although 62.7% of outpatient visits included tobacco screening, only 20.9% of current tobacco users received counseling and 7.6% received a prescription for pharmacotherapy during their visit (13). Barriers to provider adherence to AAR practice guidelines are well-documented (i.e., time restraints) (7). As such, innovation in implementing AAR clinical practice guidelines is needed to facilitate the delivery of evidence-based smoking cessation treatments, especially in clinical populations disproportionately burdened by tobacco use.

Advances in electronic health records (EHR) have allowed the delivery of population health interventions in clinical settings. EHRs are a means for systematically obtaining and electronically storing details about a patient's health history, including demographic characteristics, clinical diagnoses, and treatment histories. A key feature of EHR is that they increase the safety and quality of health care services by allowing for the sharing of information among health care providers both within and across health institutions. Using patient health portals is an innovative strategy for proactively offering health promotion information and guidance at the health system level. Patient portals are tied to EHR and are secure online tools specifically designed to help patients access and manage their health history, including communicating with their providers (14). Patient portals allow patients to view a subset of the more extensive health-related information contained in their EHR (e.g., diagnoses, medication lists, appointments). In addition, specific information can be provided to patients via their patient portals outside of a traditional health care visit. Patient health portals can be accessed via computers or internet-enabled smartphones (15, 16). According to the American Hospital Association, 93% of hospitals provide patients access to electric health records (EHRs) *via* patient portals (17). Data from the National Cancer Institute found that 52% of patients reported being offered access to their patient portals by their providers (18). Enrolling in newly available patient portal systems has demonstrated effectiveness in increasing patient-provider communication access to health information and delivering evidence-based preventive services (14, 18).

To date, a small number of randomized controlled trials have used the EHR to identify an entire population of smokers and proactively engage them in treatment (14, 18–21). Proactive engagement can be defined as the systematic targeting of all smokers in a population (e.g., health care system). Proactively calling smokers in the general population to offer free quitline counseling increases quit attempts and cessation rates (22). Several trials have demonstrated the benefit of population-based outreach efforts compared to standard clinical practice on receipt of smoking cessation counseling or medications (range 12.8–14.5 vs. 5.1–7.3%, respectively), and abstinence rates (range 5.3–13.5 vs. 1.1–10.9%, respectively) (20). A few studies have evaluated the reach and feasibility of delivering health promotion interventions *via* patient portals (14, 23). However, few have tested the use of patient portals to offer population-level smoking cessation treatments consistent with the AAR framework that directly links smokers to a state tobacco quitline and does not require trained clinical staff to implement.

Despite the early promise, the potential of patient portals as a health intervention delivery system will be limited by patient enrollment, especially among patients impacted by the digital divide (24). Integrating the promotion of patient portal use into routine primary care practices and offering assistance in enrollment may increase the use of patient portals (25). Patient navigation (PN) is a recognized and evidence-based approach for reducing health inequalities (26) and has been shown to increase patient access to health care services (27). The primary role of the PN is to address patients' informational, emotional, and practical needs associated with accessing health care. A recent meta-analysis of randomized clinical trials of PN interventions demonstrated that, compared to usual care, patients who received PN were significantly more likely to access health screening (OR 2.48, *p* < 0.00001) and to attend a recommended care event (OR 2.55, *p* < 0.01) (27). However, more research is needed to evaluate whether PN can increase patient portal access among patients with low health literacy, racial/ethnic minorities, and patients with limited computer skills; thereby, helping to realize the potential of patient portals for widespread delivery of smoking cessation interventions.

There is strong evidence that health care providers offering screening, brief counseling, and pharmacotherapy reduces tobacco use (6). However, consistent delivery of provider-led tobacco cessation treatments in clinical settings is challenging (28). Our multi-disciplinary team proposes Mi QUIT CARE, an innovative implementation strategy for providing guideline-concordant tobacco treatment in an urban FQHC system to address this implementation barrier. Informed by the socioecological framework (29), my Mi Quit Care includes electronically delivering the AAR brief smoking cessation intervention via the patient portal (8–12). This approach will allow for proactively linking all identified smokers to the state tobacco quitline (30). Further, we will provide patient navigation to reduce barriers to engagement with the patient portal and the state tobacco quitline (26, 27). Patient portals represent a promising strategy for enhancing access to smoking cessation treatments among low-income smokers. However, developmental work is necessary before a full implementation trial to increase this approach's feasibility, acceptability, and cultural appropriateness. As such, the specific aims of this formative study are to:

Examine the burden of tobacco use (smoking prevalence) and its influence on pulmonary health inequalities (lung cancer, COPD, and asthma) in the patient populations served by MSHC.To evaluate among MSHC patients and health care providers, knowledge, attitudes, barriers, and facilitators related to smoking cessation, engagement with the tobacco quitline, linkage to the tobacco quitline via a patient health portal, and receipt of patient navigation to facilitate access to the tobacco quitline.To evaluate the use of tailored communication strategies and patient navigation to increase patient portal uptake among patients receiving care at MSHC.To test the acceptability, feasibility, and capacity of a federally qualified health care system to deliver Mi QUIT CARE, an evidence-based and multi-level intervention to increase engagement with the quitline via the patient portal.

## Materials and Methods

### Study Design

Study design and procedures are described below according to study-specific aims (see Figure 1). Qualitative (examining implementation) and quantitative methods (following a randomized controlled trial design) will be used in this hybrid effectiveness-implementation pilot design (31) to evaluate the feasibility and acceptability of a novel delivery system (patient portal) in increasing access to effective smoking cessation treatments. To ensure the scientific rigor and reproducibility of the study, we will use an established evaluation framework, RE-AIM (32). RE-AIM is a planning and evaluation model that addresses five dimensions of the individual- and setting-level outcomes critical to program impact and sustainability: Reach, Effectiveness, Adoption, Implementation, and Maintenance (32). RE-AIM was selected because it is a valuable framework for planning, implementing, and evaluating practice-based interventions to improve external validity.

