All English-speaking adult patients at three MSHC locations (Main, South Shore, and Englewood) who smoke and are enrolled in the UI Health Patient Portal will be eligible for this pilot test. An equal number of patients (total *N* = 100) will be randomly selected from each location for the feasibility trial using a software program developed by programmers at the University of Illinois at Chicago. Human subject approval will be obtained before data collection, and formal informed consent obtained from participants.

Figure 3 displays an overview of the activities to be conducted in Aim 4 of the study. The intervention will be based on the 3 A's framework (Ask-Advise-Refer, [AAR]) (9, 11, 12). In the first phase of this aim, we will *Ask and Identity, All Smokers*. Project staff will review the electronic health record of the six participating clinic locations to identify all current smokers. Any patient without documented smoking status will be flagged for input during the subsequent clinical encounter. Next, we will *Advise a Quit Attempt*. A random selection of all smokers enrolled in the patient portal will be sent a signed letter from their provider via the portal. The letter will describe health risks associated with smoking, explain the availability of free treatments, strongly encourage the patient to make a quit attempt, and inform them that they will be receiving a call from the Illinois Tobacco Quitline. Patients will be informed that the ITQL will provide free smoking cessation counseling and nicotine replacement therapy (nicotine patches). An automated text or email message with a hyperlink to the portal login page will be generated and sent to patients to alert them of the message from their providers.

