### Data Analysis

Consistent with RE-AIM (32), our primary outcomes will include Reach and Impact (Reach x Efficacy). We will obtain feasibility data from the patient portal. First, we will assess which patients received (opened) an electronically generated message from their providers advising them to make a quit attempt, describing free stop smoking services from the ITQL, and informing them about an upcoming call from the ITQL. All patients will be allowed to opt into the proactive ITQL counselor call. We will evaluate what percentage of patients opt-in to treatment and the demographic factors associated with the decision to accept linkage to the ITQL. Next, we will assess the percentage of patients who opted-in to treatment and were subsequently reached by the ITQL. Finally, we will evaluate the percentage of patients who engaged in stop smoking treatment (participated in more than 1 counseling call) and their quit outcomes. Patient receipt of treatment and self-reported quit rates will be obtained from the ITQL. The ITQL will provide a monthly report on patient engagement and quit rates. Statistical analyses (multivariable logistic regression models) will be conducted to determine demographic factors (age, race, gender, clinic) associated with receipt of the provider message and advice to quit smoking, receipt of treatment by the ITQL, and quit rates. One of our smoking cessation patient navigators will contact patients who opted-in to linkage to the ITQL and who were not reached by an ITQL counselor. Patient navigators will record barriers to quitline engagement that will be qualitatively analyzed. Data from this aim will refine implementation strategies and procedures in preparation for a fully powered randomized controlled trial.

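### The article claims a randomized controlled trial design, but no aim describes random allocation, so Impact (Reach x Efficacy) in Aim 4 can only be an uncontrolled description

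*Protocol article*

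**What the plan says.** The Study Design section of the protocol article describes the quantitative part of the study in these words: "quantitative methods (following a randomized controlled trial design) will be used in this hybrid effectiveness-implementation pilot design".

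The Abstract states the objective as follows: "We aim to evaluate the efficacy of a novel delivery system (patient portal) for increasing access to smoking cessation treatment". The Data Analysis section fixes the primary outcomes: "our primary outcomes will include Reach and Impact (Reach x Efficacy". Efficacy is not defined further there.

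For Aim 4, Study Procedures gives the eligible group as "All English-speaking adult patients at three MSHC locations (Main, South Shore, and Englewood) who smoke and are enrolled" in the portal, and then says "An equal number of patients (total *N* = 100) will be randomly selected from each location". On delivery it says "A random selection of all smokers enrolled in the patient portal will be sent a signed letter from their provider via the portal". On outcomes, Data Analysis says "Patient receipt of treatment and self-reported quit rates will be obtained from the ITQL".

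For Aim 3, Study Procedures names three clinics that run the enrollment campaign (Main, South Shore, Englewood) and three that wait (Back-of-the-Yards, Cicero, Humboldt Park). It compares them on portal enrollment. How the clinics were assigned is not stated.

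**The concern.** Random selection and random allocation do different work. Selecting 100 smokers at random from a clinic list makes the sample represent that list. It does not create two groups whose difference estimates an effect. The article claims the second and describes the first.

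A reader who takes the design statement at face value will read the Efficacy half of Impact as a difference from a control group. Aim 4 gives a proportion who quit in one group of smokers, all selected to be sent the letter. That proportion includes any who would have quit or called the quitline without it. The correct interpretation of one of the two named primary outcomes is at stake, together with the efficacy claim in the Abstract.

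**Working it through.** The article gives no alpha, power, effect size or allocation ratio for the 100 patients, so there is no sample-size figure to reproduce. The main check is to look for an allocation step, aim by aim.

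| Aim | What is done | Use of chance | Comparison group | Outcome |
|---|---|---|---|---|
| 1 | Analysis of health records | none | none allocated | smoking prevalence, lung disease |
| 2 | Focus groups and interviews | none | none | qualitative |
| 3 | Enrollment campaign | none described; clinics named | three waitlist clinics | portal enrollment |
| 4 | Provider letter and quitline referral | random sampling of 100 | none planned | opened, opted in, reached, engaged, quit |

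No row contains random allocation. The only row with a control group (Aim 3) has an outcome that says nothing about quitting. The regressions planned for Aim 4 use age, race, gender and clinic as factors and have no treatment-group term. The Abstract, Data Analysis and Conclusions all place the randomized trial after this study.

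**What Aim 4 can give.** Reach multiplied by the observed quit proportion can be calculated. As an example of its precision, 13 quitters among 100 give 13%, with an exact (Clopper-Pearson) 95% interval of 7.1% to 21.2%. This treats the 100 as a simple binomial sample and ignores the division by clinic.

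**What it cannot give.** The Introduction (Tobacco Cessation Treatments) cites abstinence of 5.3% to 13.5% with outreach and 1.1% to 10.9% with standard practice. Assume, for illustration only, that the unknown background rate lies in the second range. Then effect = observed rate - background rate:

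- Observed 13.5%: 13.5 - 10.9 = +2.6 to 13.5 - 1.1 = +12.4 points.
- Observed 5.3%: 5.3 - 10.9 = -5.6 to 5.3 - 1.1 = +4.2 points.

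At the lower rate even the sign is open. This is before sampling error.

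**Would splitting the 100 rescue the claim?** Assume 50 per arm and two-sided alpha 0.05, with q = 1 - p, p̄ the mean of p1 and p2, and q̄ = 1 - p̄:

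- power = Φ{[|p1 - p2|√50 - 1.96√(2p̄q̄)] / √(p1q1 + p2q2)}
- n per arm for 80% power = [1.96√(2p̄q̄) + 0.84√(p1q1 + p2q2)]² / (p1 - p2)²

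| Abstinence rates | Power, 50 per arm | n per arm for 80% |
|---|---|---|
| 5.3% vs 1.1% | 22% | 275 |
| 13.5% vs 10.9% | 6% | 2,487 |
| 13.5% vs 1.1% (most favourable) | 67% | 68 |

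A control arm would make the effect estimable, but only imprecisely at this size. Relabelling is the proportionate remedy.

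**The case against.** The best defence is that this is openly a pilot. The article calls the study formative and developmental, and the stated purpose in Study Design is feasibility and acceptability. The Abstract speaks of efficacy in increasing access to treatment, not in producing abstinence. The Conclusions promise only initial data on reach and effectiveness. No between-group test in Aim 4 hangs on the design label. All of this is correct, and it is why the remedy is a change of wording. It does not make the design statement true or define Efficacy.

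Several stronger readings are tempting and do not hold.

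- A reader might infer that Impact cannot be computed at all. It can, as a description; only a controlled effect is out of reach.
- A reader might infer that the pilot quit rate will be carried into the later trial as an effect size and will inflate it. The article says only that the data will refine strategies and procedures.
- A reader might use the cited ranges to say what share of quitting would happen anyway. Pairing low with low and high with high gives 1.1/5.3 = 21% and 10.9/13.5 = 81%. Cross-pairing gives 1.1/13.5 = 8% and 10.9/5.3 = 206%. The article does not say which endpoints belong to the same trial, so no such share follows.
- A reader might infer that the Aim 3 clinics were certainly not randomized. The article names them without saying how they were assigned.
- A reader might infer that quitting can only be self-reported. Study Design commits to biochemical verification of smoking status, which conflicts with the self-report in Data Analysis.

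It can also be argued that eligible smokers who were not drawn form a group separated by chance. They do, but no comparison with them is planned, and the named source of treatment and quit outcomes is the quitline, which would not cover those never referred. The figures showing the design could not be checked. The text on Aims 3 and 4 is explicit without them.

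**Conclusion.** The point stands as a contradiction between the design claimed and the design described, with one consequence for a primary outcome. As written, Aim 4 is a single-arm feasibility pilot in a random sample. Its Impact outcome is an uncontrolled reach multiplied by an observed quit proportion. Aim 3 is a controlled comparison on portal enrollment and cannot supply Efficacy for cessation.

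This conclusion rests on the text alone and needs no numerical assumption. The ranges of +2.6 to +12.4 and -5.6 to +4.2 points show how much an uncontrolled rate leaves open. They assume that background quitting here lies within the standard-practice range of the cited outreach trials, and they are not estimates for these clinics. The documents do not support the further claim that the study's purpose is mainly causal, since feasibility and acceptability are stated plainly.

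**What to change.** 1. **Study Design.** Replace the randomized-trial wording with: single-arm feasibility pilot in a random sample (Aim 4) and a controlled comparison of intervention and waitlist clinics (Aim 3). State how the clinics were assigned, and call Aim 3 non-randomized unless they were in fact randomly assigned.
2. **Abstract and Data Analysis.** For Aim 4, replace efficacy and Impact with the proportions of all selected smokers who were reached, who were treated and who quit, each with an exact 95% confidence interval. Add that no intervention effect is estimated.
3. **Quit definition.** Reconcile the biochemical verification in Study Design with the quitline self-report in Data Analysis, and name one definition for the primary outcome.

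Items 1 and 2 cost only wording and a more modest headline claim. Item 3 is also wording if self-report is kept; if verification is kept, the means of collecting it must be described. Comparing drawn with undrawn smokers in the health record is not part of the required change: its outcome would be coarse and it would need its own ethics cover.
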